# A phase Ib/II randomized, open-label drug repurposing trial of glutamate signaling inhibitors in combination with chemoradiotherapy in patients with newly diagnosed glioblastoma: the GLUGLIO trial protocol

**DOI:** 10.1186/s12885-023-11797-z

**Published:** 2024-01-15

**Keywords:** Epilepsy, Gabapentin, Sulfasalazine, Memantine, Cancer neuroscience

## Abstract

**Background:**

Glioblastoma is the most common and most aggressive malignant primary brain tumor in adults. Glioblastoma cells synthesize and secrete large quantities of the excitatory neurotransmitter glutamate, driving epilepsy, neuronal death, tumor growth and invasion. Moreover, neuronal networks interconnect with glioblastoma cell networks through glutamatergic neuroglial synapses, activation of which induces oncogenic calcium oscillations that are propagated *via* gap junctions between tumor cells. The primary objective of this study is to explore the efficacy of brain-penetrating anti-glutamatergic drugs to standard chemoradiotherapy in patients with glioblastoma.

**Methods/design:**

GLUGLIO is a 1:1 randomized phase Ib/II, parallel-group, open-label, multicenter trial of gabapentin, sulfasalazine, memantine and chemoradiotherapy (Arm A) versus chemoradiotherapy alone (Arm B) in patients with newly diagnosed glioblastoma. Planned accrual is 120 patients. The primary endpoint is progression-free survival at 6 months. Secondary endpoints include overall and seizure-free survival, quality of life of patients and caregivers, symptom burden and cognitive functioning. Glutamate levels will be assessed longitudinally by magnetic resonance spectroscopy. Other outcomes of interest include imaging response rate, neuronal hyperexcitability determined by longitudinal electroencephalography, Karnofsky performance status as a global measure of overall performance, anticonvulsant drug use and steroid use. Tumor tissue and blood will be collected for translational research. Subgroup survival analyses by baseline parameters include segregation by age, extent of resection, Karnofsky performance status, O^6^-methylguanine DNA methyltransferase *(MGMT)* promotor methylation status, steroid intake, presence or absence of seizures, tumor volume and glutamate levels determined by MR spectroscopy. The trial is currently recruiting in seven centers in Switzerland.

**Trial registration:**

NCT05664464. Registered 23 December 2022.

## Background

Glioblastoma is one of the deadliest cancer entities, with a median overall survival in the range of just one year in population-based studies [1, 2]. The standard of care is confined to maximum safe tumor resection followed by chemoradiotherapy with the alkylating agent temozolomide and maintenance temozolomide therapy [3–5], with or without electromagnetic fields applied via scalp electrodes [6]. Tumor recurrence invariably occurs and therapeutic options are then limited [5]. Therefore, there is an urgent medical need for improved therapeutic options for patients with glioblastoma especially in the first line treatment.

The discovery of electrochemically active, oncogenic neuroglial networks in glioblastoma has sparked attempts to pharmacologically disrupt these networks [7, 8]. Glioblastoma cells interconnect to form electrochemically active networks via gap junctions [9] and these glioma cell networks synaptically integrate into neuronal circuits [10, 11]. Oncogenic calcium oscillations of tumor cell networks are activated by autonomously oscillating hub cells [12] which are present mainly in the tumor core and through activation of glutamatergic neuroglial synapses within the glioblastoma infiltration zone [10, 11]. Remodeling of distant neuronal networks can activate tumor cell networks in a vicious cycle, including through epileptic activity and by activity-dependent shedding of neuronal growth factors [13, 14]. Of note, a recent study of long-term electroencephalographic recordings in glioblastoma patients suggests high rates of sub-clinical epileptic activity which may contribute to inferior survival [15, 16].

Glioblastoma cells also synthesize large amounts of the excitatory neurotransmitter glutamate from α-ketoglutarate via branched chain amino acid transaminase-1 (BCAT-1) [17] which is released into the tumor microenvironment at high concentrations via the glutamate-cystine antiporter system x_c_ [18, 19]. This non-synaptic glutamate release may drive glioma cell invasion [20] and will likely enhance the hyperexcitability and thus the oncogenic activity of neuroglial networks [21].

Several brain-penetrating, anti-glutamatergic drugs that are clinically approved for other indications have been identified, including (i) the anti-epileptic drug gabapentin, which interferes with the binding of branched-chain amino acids to BCAT-1 and inhibits thrombospondin-1 signaling by blocking the thrombospondin receptor α2δ-1 [17, 22, 23], (ii) the anti-inflammatory drug sulfasalazine, which inhibits glutamate secretion by blocking the cystine-glutamate exchanger system x_c_ [24], and (iii) the cognitive enhancer memantine, which blocks N-methyl-D-aspartate (NMDA) type glutamate receptors, thereby inhibiting tumor cell invasion and neuroglial synapse formation [25, 26].

The omnipresence and pleiotropic functions of glutamate in glioblastoma lend rationale for a combined anti-glutamatergic therapeutic approach. The well-documented tolerability of some of these drugs supports the feasibility of a drug repurposing approach in combination with standard chemoradiotherapy. There is limited commercial interest in exploring the activity of these drugs as anti-cancer agents.

## Methods

### Study objectives

The primary objective of this study is to evaluate whether the addition of gabapentin, sulfasalazine and memantine to standard chemoradiotherapy compared to chemoradiotherapy alone improves outcome of patients with newly diagnosed glioblastoma as determined by progression-free survival at 6 months. Secondary objectives are to determine tolerability, response rates as defined by the Response Assessment in Neuro-Oncology (RANO) working group [27], progression-free survival, overall survival, seizure-free survival, patient quality of life assessed by the European Organization for Research and Treatment of Cancer Quality of Life Questionnaire C30 and Brain Tumor Module 20 (EORTC-QLQ-C30/BN20) [28, 29], caregiver quality of life utilizing the CareGiver Oncology Quality of Life Questionnaire (CarGOQoL) [30], symptom burden measured by the MD Anderson Symptom Inventory Brain Tumor (MDASI-BT) [31] and by the Neurological Assessment in Neuro-Oncology (NANO) scale [32], cognitive functioning assessed by the Montreal Cognitive Assessment (MoCA) test [33], tumor glutamate levels estimated by magnetic resonance spectroscopy as well as anticonvulsant drug and steroid use.

### Trial design

This study is an open-label, randomized, multicenter, phase Ib/II clinical trial. Following informed consent, patients who meet eligibility criteria will be randomly allocated in a 1:1 fashion to receive either a triple glutamate-targeted treatment with gabapentin, sulfasalazine and memantine plus chemoradiotherapy with temozolomide or chemoradiotherapy alone (Fig. 1). A total of 120 patients will be randomized with 60 participants in each study arm. The allocation sequence will be generated in advance using stratified block randomization with varying block sizes. Randomization will be stratified by extent of resection (gross total versus subtotal resection or biopsy). Post hoc central neuropathology review will be conducted for quality assurance. Randomized patients will enter the treatment phase and will be followed-up until death. Tumor progression will be assessed by contrast-enhanced magnetic resonance imaging every 3 months. An epileptic seizure assessment questionnaire will be filled in at every study visit and routine electroencephalography will be performed every 3 months to assess epileptic seizure control and neuronal hyperexcitability. Data bank closure will be 6 months after the last participant was randomized.

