### Statistical considerations

We considered an increase of the progression-free survival rate at 6 months (PFS-6) rate by 20% a clinically meaningful result that would warrant further exploration in a phase III clinical trial (assuming 50% survival rate following chemoradiotherapy alone and 70% with chemoradiotherapy plus gabapentin, sulfasalazine and memantine). At a power of 80% and a one-sided significance level of 10%, allowing a 10% drop-out rate, 120 patients need to be recruited (60 patients per arm) to detect this difference. The primary outcome will be assessed using a one-sided comparison of the PFS-6 proportion of patients in the two treatment arms at significance level 10% and a 90% confidence interval for the risk difference. Subgroup analyses will be based on two-sided interaction tests at a significance level 5%. The 8 subgroup analyses will not be adjusted for multiplicity and potential findings will be interpreted exploratively.

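### Data bank closure exactly 6 months after the last randomization leaves no margin for the last month-6 scans and censors overall survival earlier than the planned follow-up requires

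*Protocol article*

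**What the plan says.** Three statements in the Trial design section of the protocol article bear on this point.

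- Follow-up: "Randomized patients will enter the treatment phase and will be followed-up until death".
- Progression assessment: "Tumor progression will be assessed by contrast-enhanced magnetic resonance imaging every 3 months".
- Closure: "Data bank closure will be 6 months after the last participant was randomized".

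The abstract fixes the endpoint: "The primary endpoint is progression-free survival at 6 months". Statistical considerations analyses it as a comparison of two proportions. Study objectives lists "progression-free survival, overall survival, seizure-free survival" among the secondary objectives, and the abstract also names overall survival (OS) as a secondary endpoint. The Background gives a median OS of about one year in population-based studies. The article gives no second data cut and does not describe the closure date as a minimum or as applying to the primary analysis only.

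**The concern.** The closure date and the primary endpoint share the same 6-month horizon, so for the last participant the margin between them is zero. If scans are counted from randomization, that participant's second 3-monthly MRI falls on the closure date. If they are counted from any later start, it falls after closure. A scan that is slightly late may then miss the data bank, and a binary 6-month endpoint needs status at 6 months.

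The same date also sets the information available for OS and for PFS as a time-to-event outcome. The last participants contribute only 6 months, although the trial intends to keep following them. Later deaths would be observed, but no stated cut-off brings them into an analysis. At stake are a few primary outcomes and a noticeable share of the OS events.

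**Working it through.** **Step 1. The plan's own sample size.** The inputs are in Statistical considerations: "assuming 50% survival rate following chemoradiotherapy alone and 70% with chemoradiotherapy plus gabapentin, sulfasalazine and memantine" and "At a power of 80% and a one-sided significance level of 10%, allowing a 10% drop-out rate, 120 patients need to be recruited". With pooled variance under the null and no continuity correction:

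n per arm = [z(0.90) × √(2 × 0.6 × 0.4) + z(0.80) × √(0.5 × 0.5 + 0.7 × 0.3)]² / 0.2² = [1.2816 × 0.6928 + 0.8416 × 0.6782]² / 0.04 = 53.2, rounded up to 54.

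Inflating for drop-out gives 54 / 0.9 = 60 per arm and 120 in total. The stated figure is reproduced, with a drop-out allowance of 12 patients. The point below does not change it.

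**Step 2. Patients exposed to a late month-6 scan.** The article does not state the accrual length. I assume uniform accrual over 24 to 36 months.

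- Rate: 120/24 = 5.0 to 120/36 = 3.3 patients per month. Dividing by 52/12 weeks per month gives 1.2 to 0.8 per week, so about 1 patient per week of lag.
- Patients who have already progressed or died need no month-6 scan. With exponential PFS through the planned rates, the share progression-free at month 3 is √0.5 = 0.71 (control) and √0.7 = 0.84 (experimental), on average 0.77.
- A four-week lag (0.92 months) would touch 4.6 to 3.1 patients, and 3.6 to 2.4 after multiplying by 0.77. This counts every such scan as late, so it is an upper bound for that lag.

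**Step 3. Effect on power.** Power = Φ{[0.2√n − 1.2816 × 0.6928] / 0.6782}. Suppose the unevaluable patients come on top of a fully used drop-out allowance:

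| Extra unevaluable, total | n per arm | Power |
|---|---|---|
| 0 | 54 | 80.5% |
| 2 | 53 | 79.9% |
| 4 | 52 | 79.3% |
| 6 | 51 | 78.7% |

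The loss is 0.6 to 1.7 points. If the allowance is not used up, it absorbs these patients.

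**Step 4. Deaths available for OS.** Let A be the accrual length, c the months from last randomization to the cut, and λ = ln 2 / median. With uniform accrual and exponential survival:

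expected deaths = 120 × {1 − [exp(−λc) − exp(−λ(c + A))] / (λA)}.

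For a median of 12 months, A = 30 and c = 6: λ = 0.05776, and the share alive is (0.7071 − 0.1250) / 1.7329 = 0.336, so deaths = 120 × 0.664 = 79.7. The other cells follow in the same way (A = 30):

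| Median OS | c = 6 (as written) | c = 12 | c = 18 |
|---|---|---|---|
| 12 months | 79.7 | 91.5 | 99.8 |
| 16 months | 68.2 | 80.1 | 89.2 |
| 20 months | 59.4 | 70.8 | 80.0 |

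The cut at 18 months gives 99.8/79.7 − 1 = 25% to 80.0/59.4 − 1 = 35% more deaths. The standard error of a log hazard ratio varies roughly as 1/√deaths. It would shrink by a factor of √(79.7/99.8) = 0.89 to √(59.4/80.0) = 0.86, so confidence intervals narrow by about 11% to 14% on the log scale.

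**Step 5. Sensitivity.** With accrual of 18 to 42 months and medians of 12 to 18 months, 27% to 57% of the 120 patients are alive and censored at closure, leaving about 88 to 51 deaths. The share who could not have reached 12 months of follow-up is 6/A: 25%, 20% and 17% for accrual of 24, 30 and 36 months. Minimum follow-up is 6 months against a cited median of about 12, so about half.

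**The case against.** The strongest reply is that the two statements do not conflict. One describes how long patients are followed and the other when data are frozen. Follow-up to an event, cut at a common calendar date, is ordinary administrative censoring. Closure may be meant only as the lock for the primary analysis; the Discussion speaks of first results by the end of 2026, which leaves room for later reports. Scan windows, the MRI starting point and data-entry rules belong in the full protocol or the data management plan, which are not shown. A cut-off can also apply to event dates, with entry completed afterwards. Finally, OS is a secondary endpoint for which the article states no power or precision target, so no target is missed.

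Much of this stands. The absence of scan windows from a condensed article is not a fault, and the choice of a later OS cut is partly a matter of judgement. Three stronger readings that a reader might infer are not supported:

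- That the passage contradicts itself. The two sentences can coexist.
- That OS follow-up is thrown away. Only the part after closure is cut; with a 30-month accrual the earliest patients would have up to 36 months.
- That the last patients' primary outcome would be carried forward from month 3. The article states no such rule.

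What the reply does not remove is the stated rule itself. It gives an exact date equal to the endpoint horizon, and no other part of the article adds a margin or a later cut. If closure means only the primary lock, the sentence needs to say so.

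**Conclusion.** The point holds at moderate severity. The effect on the primary endpoint is small: about 1 patient per week of lag before excluding those already progressed, and at most 1 to 2 points of power. It does not threaten the validity of the primary comparison, so the plan should not be read as unable to deliver its main result.

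The effect on OS is larger: about 80 to 59 deaths at closure instead of about 100 to 80 with a cut at 18 months. At the only median the article gives, about one third of patients would be censored for OS. The less favourable figures rest on longer medians, which are assumptions; they are included because the trial requires a Karnofsky score of at least 70 and eligibility for standard chemoradiotherapy, whereas the cited median is population-based. Accrual length, uniform accrual, exponential survival and the amount of scan lag are also assumptions.

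**What to change.** Replace the closure sentence with two defined cut-offs.

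1. A primary cut-off for PFS-6, once the last participant's month-6 MRI window has closed and the data are entered.
2. A separate, pre-specified later cut-off for OS and time-to-event PFS, for example 12 to 18 months after the last randomization, using the follow-up until death that is already planned. Under the assumptions in step 4, a cut at 12 months yields about 92 to 71 deaths and one at 18 months about 100 to 80.

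Fixing the later date before results are known also keeps it from looking data-driven in an open-label trial. The cost is an amendment to one sentence, a short delay to the primary lock (about two months if it were set at 8 months after the last randomization) and one additional data cut. No extra patients or procedures are needed, and the sample size stays at 120.

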**Fig. 1 Fig1:**
[figure not shown]
Schematic of the study design. Exp, experimental arm; Ctr, standard of care control arm

### Inclusion criteria

Newly diagnosed supratentorial glioblastoma according to the 2021 WHO Classification of central nervous system tumors [34]; eligible for standard chemoradiotherapy with temozolomide (hypofractionated radiotherapy regimen not allowed); age ≥ 18 years; Karnofsky performance status of ≥ 70; normal kidney and liver function; normal hematologic parameters.

### Exclusion criteria

Intent to be treated with tumor-directed therapy other than chemoradiotherapy; pregnant or breast feeding women; intention to become pregnant or father a child during study course; lack of safe contraception; clinically significant concomitant disease; known or suspected non-compliance, drug or alcohol abuse; inability to follow the procedures of the study; participation in another study with an investigational drug; contraindication for gadolinium-enhanced MRI; any prior radiotherapy of the brain; active malignancy that may interfere with the study treatment; abnormal ECG with QTc > 450 ms; previous intolerance reactions to one of the study drugs; intolerance reactions to sulfonamides or salicylates; acute intermittent porphyria; known glucose-6-phosphate dehydrogenase deficiency; concomitant therapy with digoxin, ciclosporin, methotrexate; history of exfoliative dermatitis, Stevens Johnson syndrome, toxic epidermal necrolysis, drug rash with eosinophilia and systemic symptoms (DRESS) syndrome or renal tubular acidosis.

### Study treatment

Study treatment includes oral gabapentin, sulfasalazine and memantine in the experimental study arm. Temozolomide and radiotherapy are standard of care and given to patients in both arms. Dosing of the investigational drugs in Arm A will be sought up to the maximum approved dose and will be reevaluated in an interim safety analysis after 20 patients have been randomized into the experimental arm. The investigational drugs will be given until tumor progression or withdrawal, whichever occurs first. Dosing will be reduced for at least one week in case of CTCAE grade 3 and permanently discontinued in case of CTCAE grade 4 drug-related toxicity, respectively. If toxicity is resolved to CTCAE grade 0–1, reescalation to higher dose levels is allowed. Permanent discontinuation of one out of the three investigational drugs for toxicity will not be considered treatment failure. Permanent discontinuation of two or more drugs will be considered treatment failure. For discontinuation, investigational drugs will be tapered following the reverse schedule as for the initial dosing.

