### Gabapentin

Gabapentin is approved for the treatment of epilepsy and neuropathic pain. The definite mechanism of action by which gabapentin exerts anti-convulsant and analgetic effects has not been fully clarified. Oral gabapentin will be given at a dose of 3 × 300 mg/day in week 1, 3 × 600 mg/day in week 2, 3 × 900 mg/day in week 3 and 3 × 1200 mg/day from week 4 onwards. The most common adverse events related to gabapentin include neurological symptoms, e.g. ataxia, somnolence, dizziness, vertigo, tremor, diplopia, amblyopia and nystagmus. Dosing will be permanently discontinued if DRESS syndrome attributed to gabapentin occurs.

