### Sulfasalazine

Sulfasalazine is approved for the treatment of ulcerative colitis and rheumatoid arthritis. Oral sulfasalazine will be given at a dose of 3 × 500 mg/day in week 1, 3 × 1000 mg/day in week 2 and 3 × 1500 mg/day from week 3 on. Dosing will be reduced if hematologic, liver or renal toxicity occurs and will be permanently discontinued if Lyell syndrome, Stevens Johnson syndrome or DRESS syndrome occurs.

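### The taper rule for stopped study drugs states no exception, so it is unclear whether sulfasalazine or gabapentin stopped for DRESS, Stevens Johnson or Lyell syndrome is stopped at once or stepped down

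*Protocol article*

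**What the plan says.** All places are in the protocol article.

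- **Study treatment, toxicity rule.** Dosing is lowered for at least a week at grade 3 and "permanently discontinued in case of CTCAE grade 4 drug-related toxicity, respectively".
- **Study treatment, failure rule.** "Permanent discontinuation of one out of the three investigational drugs for toxicity will not be considered treatment failure". Stopping two or more does count.
- **Study treatment, manner of stopping.** Directly after these rules: "For discontinuation, investigational drugs will be tapered following the reverse schedule as for the initial dosing". No drug and no reason for stopping is exempted.
- **Sulfasalazine.** Dosing is lowered for hematologic, liver or renal toxicity and "will be permanently discontinued if Lyell syndrome, Stevens Johnson syndrome or DRESS syndrome occurs".
- **Gabapentin.** "Dosing will be permanently discontinued if DRESS syndrome attributed to gabapentin occurs".
- **Exclusion criteria.** Patients are barred if they have a "history of exfoliative dermatitis, Stevens Johnson syndrome, toxic epidermal necrolysis, drug rash with eosinophilia and systemic symptoms (DRESS) syndrome".

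**The concern.** The taper sentence closes a run of sentences about stopping for toxicity and uses the same term, discontinuation, as the two drug sections. Those sections say when a drug is given up for good. Only the taper sentence says how stopping is done. Nothing in the article says that a drug stopped for one of the named reactions is stopped at once or without a taper.

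An investigator can therefore combine the sentences and step the drug down while the patient has the reaction for which it is being stopped. These are the reactions that the drug sections single out by name, and a past Stevens Johnson syndrome or DRESS is enough to keep a patient out of the trial. What is at stake is avoidable exposure to the suspect drug in a small number of Arm A patients. The efficacy analysis is not at stake.

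**Working it through.** **Side-by-side reading.**

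1. *Taper reading.* The drug sections give the trigger and the Study treatment section gives the manner of stopping. The two combine without contradiction, because permanence only rules out a restart.
2. *Immediate-stop reading.* In both drug sections it is the dosing itself that is discontinued, and a taper is continued dosing at a lower level. The Sulfasalazine section sets lowering the dose against discontinuing it, and the Study treatment section does the same for grade 3 against grade 4. If discontinuing began with a step down, that contrast would vanish in the first week for a patient at full dose.

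Both readings are available and no sentence in the article decides between them.

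**What the taper reading would mean per patient.** The article gives no taper length or amount to reproduce, so these follow from the dosing sections.

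Inputs:
- Sulfasalazine: 3 × 500 = 1500 mg/day in week 1, then "3 × 1000 mg/day in week 2 and 3 × 1500 mg/day from week 3 on", that is 3000 and 4500 mg/day.
- Gabapentin: 3 × 300 = 900 mg/day in week 1, 3 × 600 = 1800 mg/day in week 2, then "3 × 900 mg/day in week 3 and 3 × 1200 mg/day from week 4 onwards", that is 2700 and 3600 mg/day.
- Assumption: each reverse step lasts 7 days, as in the initial schedule, and the taper starts one step below the current dose.

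Formula: further amount = 7 × (sum of the daily doses below the current step).

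- Sulfasalazine from 4500 mg/day: 7 × (3000 + 1500) = 31,500 mg = 31.5 g over 14 days. Mean 31,500 / 14 = 2250 mg/day, 50% of full dose. Equivalent to 31.5 / 4.5 = 7.0 full-dose days.
- Gabapentin from 3600 mg/day: 7 × (2700 + 1800 + 900) = 37,800 mg = 37.8 g over 21 days. Mean 37,800 / 21 = 1800 mg/day, 50% of full dose. Equivalent to 37.8 / 3.6 = 10.5 full-dose days.

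By the time of the reaction:

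| Reaction in | Sulfasalazine | Gabapentin |
|---|---|---|
| Week 1 | none (no lower step) | none (no lower step) |
| Week 2 | 7 days, 7 × 1500 = 10.5 g | 7 days, 7 × 900 = 6.3 g |
| Week 3 | 14 days, 31.5 g | 14 days, 7 × (1800 + 900) = 18.9 g |
| Week 4 or later, at full dose | 14 days, 31.5 g | 21 days, 37.8 g |

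No day of the taper is at full dose. The article gives no incidence for these reactions and none is assumed, so the figures are per affected patient.

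**The case against.** The strongest reply is that the drug-specific sentences govern the general one. They say dosing is discontinued, they contrast this with lowering the dose, and the taper sentence still has other stops to cover, since the drugs are otherwise given until progression or withdrawal. The exclusion criterion concerns who may enrol and not how to stop a drug; if anything, it suggests the authors see these reactions as incompatible with exposure. All of this stands as support for the immediate-stop reading. It does not remove the ambiguity, because the taper sentence uses the same word, follows directly on the toxicity rules and has no qualifier.

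A second reply is that this is a condensed article and the full protocol may contain the exception. It may, and that cannot be checked here. But the point concerns a rule that the article prints without limit and does not rest on detail it leaves out.

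A reader might infer that the protocol requires tapering through DRESS or Stevens Johnson syndrome, or that an investigator who stops at once breaches it. The documents do not support either. Someone who stops at once is following the Gabapentin and Sulfasalazine sections as written, and nothing shows that a taper in these cases was intended.

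**Conclusion.** The point holds as an ambiguity in safety wording. The general taper rule has no stated exception, and the sections on permanent stops for severe reactions do not say whether it applies to them. On the taper reading, the further exposure is up to 14 days and 31.5 g of sulfasalazine, or up to 21 days and 37.8 g of gabapentin, averaging half the full dose. These figures rest on 7-day steps, a start one step below the current dose, and a patient at full dose; a reaction before full dose gives less, down to none in week 1. They show what one reading would entail and are no evidence that it is the intended one. Only Arm A patients with a named reaction are concerned. The point is worth acting on because the change is so cheap.

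**What to change.** Add one sentence after the taper rule in the Study treatment section:

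*The taper does not apply to a drug stopped for DRESS, Stevens Johnson syndrome or Lyell syndrome, which is stopped immediately; for other grade 4 drug-related toxicity the investigator decides whether to taper or stop at once.*

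The second clause is needed because naming three syndromes alone would imply that every other grade 4 toxicity must be tapered, a clinical question the documents do not settle. If the full protocol already holds such an exception, the sponsor need only confirm it.

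The stopping triggers in the Gabapentin and Sulfasalazine sections stay as they are. The cost is that the few Arm A patients who stop gabapentin for DRESS lose its taper, with seizure cover left to the investigator. The sentence changes how a drug is stopped, not whether it is stopped, so the treatment-failure rule is untouched. Enrolment, visits, PFS-6 and the sample size of 120 do not change.
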